### Primary Outcome Measure

The primary outcome measure of CALCIO is a composite of wound healing and freedom from amputation at 12 months after the first IVL procedure. Wound healing is defined as the healing status of the dominant ischemic wound of the target limb as assessed by the investigators using the categories defined in Table 3.

**Table 3 Tab3:** Definitions of wound healing status

Wound healing	
Complete	Complete epithelialization of the wound persistent for at least 14 days
Partial	Decrease of wound size > 50% compared to baseline (in largest diameter)
Unchanged	Increase or decrease of wound size ≤ 50% compared to baseline (in largest diameter)
Worsening	Increase of wound size > 50% compared to baseline (in largest diameter)

Patients who presented no wound at baseline (Rutherford category 4) are followed for the development of de novo ischemic ulcers. If such an ulcer appears after treatment, the limb will be reported separately as “worsening.”

Freedom from amputation will be assessed by considering both minor (digital, metatarsal) and major (below or above the knee) amputations; however, amputations that had been planned before the first IVL treatment will be reported separately. For patients who receive an amputation, healing of the stump will be reported.

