## Statistical Analysis

CALCIO is a single-arm study that will use mainly descriptive statistics to report the outcome measures. The target of 400 participants was not determined through a formal sample size calculation but was assessed by the Steering Committee as a sufficiently large sample to provide meaningful information on the treatment’s effectiveness while remaining achievable within the planned enrollment period. All participants who were planned to receive IVL will be included in the intent-to-treat (ITT) population, regardless of whether they received the planned procedure. In contrast, the modified intent-to-treat (mITT) population will only include participants who received IVL treatment.

The results of the primary outcome measure will be presented using summary statistics and a 95% confidence interval (CI). For time-to-event outcome measures (amputation-free survival) and (CD-TLR-free survival), median time-to-event and 95% CI will be calculated using the Kaplan–Meier estimator, while the impact of different covariates will be assessed using a stratified log-rank test and an univariable Cox proportional hazard regression. Following that, covariates with *p* values < 0.1 and ≤ 20% missing data will be included in a multivariable Cox proportional hazards regression model, while variables with p values < 0.05 will be retained in the model after backward elimination or if they contribute to the predictability of the model. All variables that were not included in the model due to extensive missing data will be listed. All other statistical tests will be based on a significance level of 5%, and estimates will be presented using 95% bilateral CIs. No adjustment for multiple testing will be done. In the analyses of time-to-event outcomes, data will be censored at the last time the patients’ status was assessed.

In general, no imputation of missing data is planned for the analyses, and missing observations will be presented as a percentage of the total. However, for the primary outcome measure, depending on the number of deceased and lost-to-follow-up participants before 12 months, a sensitivity analysis may be performed.

Given the absence of planned confirmatory hypothesis testing, findings should be considered exploratory. The statistical analysis will be conducted using the latest available versions of R and RStudio.

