## Discussion

IVL is a relatively recent technology with an expanding evidence base in claudicant patients demonstrating a favorable safety profile and significant luminal gain in calcified lesions; however, evidence in patients with CLTI remains limited. A recent single-center retrospective study on CLTI patients receiving IVL plus drug-coated balloon reported promising 12-month outcomes, with 92% freedom from CD-TLR, 98% freedom from major amputation, and 89% overall survival [20].

Despite the consensus that vascular calcification hinders clinical outcomes of endovascular interventions, European and American guidelines on the management of PAD offer limited, non-specific direction on revascularization strategies for severely calcified lesions and do not consistently address IVL or other plaque-modifying techniques [1, 2]. Reimbursement for IVL remains variable across healthcare systems, which likely constrains routine adoption.

In the UK, however, the National Institute for Health and Care Excellence (NICE) released its guidance on IVL for calcified arteries in PAD in 2024 (www.nice.org.uk/guidance/ipg780). Acknowledging “an unmet need for a safe and effective endovascular option for treating heavily calcified arterial lesions when surgery is unsuitable,” the NICE recommendations state that IVL can be used with special arrangements for clinical governance, consent, and audit or research. The existence of such guidelines is directly reflected in clinical practice, as a larger number of patients have access to the procedure in the UK compared to other countries. However, while the NICE guidance is based on the conclusion that IVL is safe and associated with a reduced need for stenting, it also highlights a lack of evidence regarding long-term patient outcomes. NICE specifically encourages further research to include details on patient selection (including lesion location and stenosis severity), adjunctive interventions, the need for repeat revascularization, patient-reported quality of life, amputation, and mortality.

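### The plan does not say how death before 12 months counts in the primary outcome, appears to treat it as missing, and leaves the only check optional

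*Protocol article*

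**What the plan says.** The Primary Outcome Measure section states: "The primary outcome measure of CALCIO is a composite of wound healing and freedom from amputation at 12 months after the first IVL procedure". Healing is the investigator's grading of the dominant ischemic wound in four categories (Table 3). Freedom from amputation considers minor and major amputations, with those planned before IVL reported separately. Death is neither a component of the composite nor named as a failure.

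The Statistical Analysis section reports this outcome by summary statistics with a 95% CI and gives no denominator. On missing data it says: "In general, no imputation of missing data is planned for the analyses, and missing observations will be presented as a percentage of the total". It then makes one exception, for the primary outcome: "depending on the number of deceased and lost-to-follow-up participants before 12 months, a sensitivity analysis may be performed". The article gives no threshold that would trigger this analysis.

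Survival enters two secondary time-to-event outcomes, amputation-free survival and CD-TLR-free survival. Neither includes wound healing.

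**The concern.** A patient who has died has no wound status at 12 months. The only sentence on deaths in the primary outcome puts them beside losses to follow-up, as an exception to a no-imputation policy. Read naturally, deaths drop out and the headline proportion describes patients alive and assessed.

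Death is not an ordinary missing value. It ends the possibility of healing and is related to the severity of the disease; the Abstract itself links severe calcification to amputation and death. A proportion among survivors answers a different question from the proportion of treated patients who are alive with a healed wound and an intact limb at one year. The Discussion expects the results to inform guidelines and reimbursement, where the two could easily be confused.

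The sensitivity analysis is also conditional on the number of deaths and losses. Whether readers see the check would be decided once those counts are known, in a single-arm study with an investigator-reported primary outcome.

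**Working it through.** **Nothing to reproduce.** The article states "The target of 400 participants was not determined through a formal sample size calculation" and gives no expected success, mortality or loss rate. What follows illustrates size only.

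**Inputs**
- N = 400, the planned sample, taken as all treated.
- d, the fraction dead by 12 months: 11% (100% − 89%), from the single-center retrospective cohort cited in the Discussion ("92% freedom from CD-TLR, 98% freedom from major amputation, and 89% overall survival"). It is the only 12-month mortality figure in the article. Assumed alternatives: 5% and 20%.
- p, the success proportion among patients alive and assessed: assumed, 50% to 80%.
- Losses: none at first, then an assumed 10%.

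**Deaths, no losses**

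With death as non-success, the proportion over all treated patients is p(1 − d). If deaths are dropped, the reported figure is p. The gap is p × d. The 95% CI half-width is 1.96 × √(p(1 − p)/n), with n the number assessed.

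At d = 11%, deaths = 400 × 0.11 = 44 and n = 356. For p = 60%: 0.60 × 0.89 = 53.4%; gap 0.60 × 0.11 = 6.6 points; half-width 1.96 × √(0.24/356) = 5.1 points.

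| Success among assessed | Death as non-success | Gap (points) | CI half-width (points) |
|---|---|---|---|
| 50% | 44.5% | 5.5 | 5.2 |
| 60% | 53.4% | 6.6 | 5.1 |
| 70% | 62.3% | 7.7 | 4.8 |
| 80% | 71.2% | 8.8 | 4.2 |

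At d = 5% (n = 380) the gap is 2.5 to 4.0 points and does not exceed the half-width (5.0 to 4.0 points). At d = 20% (n = 320) it is 10 to 16 points, against 5.5 to 4.4.

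The gap p × d assumes that every death leaves the denominator. If patients amputated before dying are kept as failures, it is smaller.

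**Losses alone**

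Take p = 60% among the 90% assessed, and let q be the success rate in the 10% lost. The error is 0.60 − (0.90 × 0.60 + 0.10 × q):
- q = 40%: 0.60 − 0.58, 2 points too high
- q = 60%: no error
- q = 80%: 0.60 − 0.62, 2 points too low

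The direction is therefore not fixed.

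**Deaths and losses together**

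With 44 deaths and 40 losses, 316 are assessed. At p = 60% there are 0.60 × 316 = 189.6 successes. With deaths as non-success, the whole-cohort proportion lies between 189.6/400 = 47.4% (every lost patient fails) and (189.6 + 40)/400 = 57.4% (every lost patient succeeds).

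**The case against.** The strongest reply is that the article never states a survivors-only analysis. No denominator is given. Showing missing observations as a percentage of the total is compatible with missing as its own category over all patients, and counting death as non-success would be part of an endpoint definition rather than imputation. This stands: survivors-only is an inference. It does not remove the problem, because under either reading the role of death and the denominator of the CI remain undefined.

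Three stronger readings are tempting, and the document does not support them. First, a reader might infer that a patient amputated at month 3 who dies at month 9 is discarded. No section says so; that failure is already known and could still be counted. Second, a reader might infer that the handling of missing data as a whole biases success upward. That holds for deaths only, and only relative to treating death as non-success, which the composite does not state. Third, 89% survival might be taken as the study's expectation. It is an external result in patients who also received a drug-coated balloon.

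The comparison with the half-width also depends on having no losses. With 40 losses who all succeed, the difference from 60% is 60 − 57.4 = 2.6 points, below the half-width of about 5.4 points at n = 316. That is the extreme favorable case; the opposite extreme gives 60 − 47.4 = 12.6 points.

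Amputation-free survival means mortality is not hidden, and findings are labelled exploratory. Both soften the point. But no listed outcome combines healing with survival, and a descriptive headline figure still needs a defined denominator.

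Finally, the method of a sensitivity analysis is commonly left to the SAP, so its absence here is not criticized. The grouping of deaths with losses and the optional status of the check are stated in the article itself.

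**Conclusion.** The point holds in a limited form. How death before 12 months counts in the primary outcome is undefined, the text appears to treat it as missing, and the one safeguard is optional and data-dependent.

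If deaths are dropped, success is overstated relative to death as non-success. At the only mortality figure in the article, and with no losses, this choice moves the result by more than its sampling error; at 5% mortality it does not. The size rests on assumed success rates and a borrowed mortality rate, so it shows scale and does not predict the study's bias. For losses, neither direction nor size can be stated. This should be fixed and is cheap to fix, but it does not invalidate the study.

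**What to change.** Before 12-month data are analysed, state in the plan:

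1. The denominator of the primary proportion: all treated patients (the mITT population).
2. Death before 12 months counts as non-success.
3. An amputation known to have occurred before death or loss counts as failure on that component. Amputations planned before IVL stay reported separately.
4. The sensitivity analysis is always performed, with best-case and worst-case bounds for losses.
5. The proportion among patients alive and assessed is reported as supportive and labelled as such.
6. How Rutherford category 4 patients without a baseline wound, and wounds graded as partially healed, enter the composite. Without this, a success proportion over all treated patients cannot be computed.

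Multiple imputation for losses, and Aalen-Johansen cumulative incidence of healing and amputation with death as a competing event, are optional additions.

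The cost is a few sentences and a few extra tables, with no new data. The reported success rate will probably be somewhat lower.

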## Discussion

IVL is a relatively recent technology with an expanding evidence base in claudicant patients demonstrating a favorable safety profile and significant luminal gain in calcified lesions; however, evidence in patients with CLTI remains limited. A recent single-center retrospective study on CLTI patients receiving IVL plus drug-coated balloon reported promising 12-month outcomes, with 92% freedom from CD-TLR, 98% freedom from major amputation, and 89% overall survival [20].

Despite the consensus that vascular calcification hinders clinical outcomes of endovascular interventions, European and American guidelines on the management of PAD offer limited, non-specific direction on revascularization strategies for severely calcified lesions and do not consistently address IVL or other plaque-modifying techniques [1, 2]. Reimbursement for IVL remains variable across healthcare systems, which likely constrains routine adoption.

In the UK, however, the National Institute for Health and Care Excellence (NICE) released its guidance on IVL for calcified arteries in PAD in 2024 (www.nice.org.uk/guidance/ipg780). Acknowledging “an unmet need for a safe and effective endovascular option for treating heavily calcified arterial lesions when surgery is unsuitable,” the NICE recommendations state that IVL can be used with special arrangements for clinical governance, consent, and audit or research. The existence of such guidelines is directly reflected in clinical practice, as a larger number of patients have access to the procedure in the UK compared to other countries. However, while the NICE guidance is based on the conclusion that IVL is safe and associated with a reduced need for stenting, it also highlights a lack of evidence regarding long-term patient outcomes. NICE specifically encourages further research to include details on patient selection (including lesion location and stenosis severity), adjunctive interventions, the need for repeat revascularization, patient-reported quality of life, amputation, and mortality.

Designed to specifically address these evidence gaps, CALCIO intends to complement the existing literature by collecting prospective data on the use of IVL in real-world CLTI practice. The findings are expected to contribute to future discussions on the role of IVL in clinical guidelines and inform reimbursement considerations for its use in CLTI patients. The study was received very positively by the community, with over 50 sites expressing interest in participating.

Patient enrollment for CALCIO opened in July 2024 and is planned to continue until July 2026. The follow-up period is expected to end in July 2028. At the time of manuscript submission, 38 sites from 8 countries, including 14 in the UK, were participating in the study and 357 patients had been enrolled, including 182 in the UK.

## Conclusions

CALCIO is the first large-scale study on the use of IVL for patients with CLTI. By collecting robust real-world data on clinical outcomes that are crucial to patients, in particular wound healing, freedom from amputation, and quality of life, CALCIO aims to provide pivotal information on the long-term impact of IVL to inform clinical practice guidelines and support decision making on optimal treatments and thereby improve outcomes for CLTI patients.
